#### Secondary outcomes

28-day intubation rate (intubation is defined as endotracheal intubation and receiving invasive mechanical ventilation);28-day all-cause mortality(defined as death caused by all kinds of diseases within 28 days after randomisation);Change in the daily PaO_2_/FiO_2_ ratio (measured every morning around the same time) during intervention;Change in daily Borg scale score;Daily and total position changing time;Change in daily ROX index: SpO_2_/FiO_2_ to respiratory rate;Number of hours receiving HFNO therapy;Number of hours receiving noninvasive mechanical ventilation and invasive mechanical ventilation;Treatment failure rate (defined as patients who receive noninvasive, invasive ventilation or die after taking assigned positions);The incidence of adverse events;Length of hospital stay and ICU stay.Hospitalisation cost.

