### Indications for terminating the intervention

When the patient’s flow velocity is < 30 L/min and the PaO_2_/FiO_2_ ratio is > 300 mmHg for 6 h [38];The patient can maintain SpO_2_ at 92%–96% [39] with a respiratory rate no more than 25–30 times per minute while using conventional oxygen therapy (nasal prongs, facemask with or without reservoir or Venturi mask with less than 8 litres per minute and the fraction of inspired oxygen less than 35%).The patient’s condition worsens, noninvasive ventilation or endotracheal intubation is needed (see more in “Indications for noninvasive ventilation” and “Indications for endotracheal intubation” section) or death occurs.

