### Data collection and management

The outcomes will be measured during the intervention and 28 days after the patients are enrolled in the group. The data on the duration of different respiratory support, hospital and ICU lengths of stay, and hospitalisation cost will be collected at discharge or the 28th day after enrolment, whichever occurs first. (The data collection schedule is shown in Table 1). Trained nurses will assess the Borg scale score and fill in the bedside inspection forms (Additional file 6) with average vital signs within 3 min at each allotted timepoint and position change time of each round. Supervisors will examine and transcribe inspection forms every day. Two trained researchers who do not know patients’ allocations will check and collect all other data extracted from the electronic medical record system, including data on withdrawn patients. The main researchers will explain every detail of the parts each researcher is responsible for through online or physical training with a set of standard teaching materials, check the training effect through a test, and give one-to-one guidance to every researcher according to their results.

**Table 1 Tab1:** Data collection schedule

Study Period	Timepoint	Assessments
Enrolment	Day 0–1	Eligibility
		Informed consent
Allocation		Baseline information
		PaO_2_/FiO_2_ ratio after receiving HFNO therapy for 2 h
Post-allocation	During interventions (Day 1–termination)	Vital signs
		PaO_2_/FiO_2_ ratio
		Borg scale
		Position changing time (experimental groups only)
		ROX index
		Special treatments
		Respiratory support
		Adverse events
	At discharge/Day 28	Hospitalisation cost
		Number of hours using HFNO
		Number of hours using advanced respiratory support mode
		Number of hours using conventional oxygen therapy
		Length of hospital and ICU stay
Close-out	At Day 28	Death
		Endotracheal intubation

The confidentiality of the data will be preserved when the coded, anonymised data are transmitted and stored at the location of the statistician in charge of the final analysis.

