### Statistical methods for the primary and secondary outcomes

Analysis of variance will be used for ventilator-free days in 28 days, the number of hours using HFNO, noninvasive ventilation, invasive mechanical ventilation, length of hospitalisation, and hospitalisation cost. When it indicates that at least one group is significant, the Bonferroni correction will be applied.

For the 28-day mortality rate and 28-day intubation rate, we will conduct a survival analysis with the Kaplan-Meier method. We will compare the mortality and intubation rates of the three study groups using a log-rank test. We will use the Cox proportional hazards model to detect the relationship between diagnosis, onset time, PaO_2_/FiO_2_ ratio change, the duration of changing positions, and total position changing time.

Other secondary outcomes, such as the change in the PaO_2_/FiO_2_ ratio, ROX index, Borg scale score within the groups, will be compared with a paired repeated measures analysis of variance or generalised estimating equation based on the integrity of the data. The incidence of adverse events will be analysed using either the chi-square test or Fisher’s exact test. Univariate and multivariate analyses of risk factors for prone position failure will be performed with logistic regression.

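### Daily PaO2/FiO2, ROX and Borg series end on recovery or failure, and the planned repeated-measures ANOVA or GEE does not allow for this, so change estimates can be biased in either direction

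*Protocol article*

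**What the plan says.** **Window.** The Secondary outcomes section limits change in daily PaO2/FiO2 to readings "measured every morning around the same time) during intervention". Table 1 (Data collection and management) places PaO2/FiO2, Borg and ROX together in the row "During interventions (Day 1–termination").

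**What ends the window.** The section on indications for terminating the intervention gives three routes:
- low flow, when in addition the PaO2/FiO2 "ratio is > 300 mmHg for 6 h";
- adequate saturation "with a respiratory rate no more than 25–30 times per minute while using conventional oxygen therapy";
- deterioration in which "noninvasive ventilation or endotracheal intubation is needed", or death.

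The separate list of indications for noninvasive ventilation includes ROX thresholds (2.85, 3.47 and 3.85 at 2, 6 and 12 h), so a low ROX can itself end the series.

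**Analysis.** The statistical methods section says that change in these measures "will be compared with a paired repeated measures analysis of variance or generalised estimating equation based on the integrity of the data". It describes this as change inside each group and spells out no between-arm contrast.

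**Missing data.** Methods for additional analyses provides multiple imputation for withdrawn patients. The withdrawal criteria cover refusal, too little positioning time, mid-trial discharge and a staff judgement of serious harm. They do not list recovery without discharge, noninvasive ventilation, intubation or death.

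**The concern.** The protocol fixes the measurement window, the stopping rules and the methods, and the three do not fit together. A patient's series is short because the patient did well or did badly. The patients left on a later day are a selected middle group, and a position that changes recovery or escalation also changes who is in that group.

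Neither named method corrects for this. Standard repeated-measures ANOVA needs a full series, so it drops early recoverers and early failures. Unweighted GEE keeps their days before exit but in general needs missingness unrelated to the outcome. Choosing between the two by data completeness leaves both problems in place. At stake is whether the reported course of oxygenation, ROX and dyspnoea describes the randomised groups or only those who stayed on high-flow oxygen.

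**Working it through.** **The plan's own figure.** The protocol gives no daily means, SDs or exit rates, so there is no figure to reproduce for these outcomes. The sample size of 486 concerns ventilator-free days and does not bear on this point.

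**Model used for illustration.** All inputs are assumptions. Daily PaO2/FiO2 = baseline + patient slope × day + noise. A series stops once a reading is above 300 or below 100 mmHg. The true day-7 arm difference is 7 × (difference in mean slope).

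- Set-up A: baseline 200 (SD 45), slopes 8 v 16 mmHg/day, slope SD 10, noise SD 20. By design 7 × 8 = 56.
- Set-up B: baseline 190 (SD 40), slopes 5 v 10, slope SD 20, noise SD 15. By design 7 × 5 = 35.
- Set-up C: as A, but slopes 5 v 10. By design 35.

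**Day-7 arm difference, 1,500 per arm (mmHg)**

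| Set-up | True in run | Complete cases | GEE, independence | GEE, exchangeable | Mixed, random intercept | Mixed, random slope |
|---|---|---|---|---|---|---|
| A | 56 | 21 | 21 | 37 | – | 57 |
| A, eligible baselines | 54 | 32 | 24 | 38 | – | 53 |
| A, eligible baselines | 56 (design) | – | 26 | 40 | 41 | 56 |
| Re-run, true treated-arm change 112 as in A | 58 | 26 | 26 | 43 | 44 | 59 |
| C | 33 | 20 | 17–24 (both GEEs) | | – | 32 |
| B | 28 | 4 | 2–9 (both GEEs) | | – | 27 |

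The true values vary by chance. In A the SD of day-7 change is about √(70² + 20²) = 72.8, so the standard error of the arm difference is 72.8 × √(2/1500) = 2.7. In B it is √(140² + 15²) × √(2/1500) = 5.1. All rows agree with their design values.

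**Set-up B with 200,000 per arm, patients still observed only.**
- Day 3: true 14.8, seen 9.3, with 81% (control) and 80% (treated) still observed.
- Day 7: true 34.5, seen 6.9, with 47% and 44% still observed. 6.9/34.5 = 20% of the true difference remains.
- Recovery exits only: 17.1 on day 7. Failure exits only: 22.1.

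**Within-group change.** In A the treated arm's true change is 7 × 16 = 112 mmHg. Complete cases showed 55 in one run and 68 in another.

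**No true difference.** With slopes equal but failure exits at 130 mmHg in control and 100 in the treated arm, the difference seen on day 7 was about −10 mmHg. Exchanging the arm labels gives about +10, so the sign depends on which arm's failures leave sooner. In a further run on assumed inputs, a true difference of about 2 mmHg appeared as −3 to −15.

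**The case against.** **The arm comparison is read in.** The methods text speaks of change inside each group. This stands as a limit on wording. It does not remove the problem, because within-group change is distorted too and the stated objectives compare positions.

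**The sizes are made up.** No input comes from the documents. Real termination needs low flow together with high PaO2/FiO2 for 6 h, or stability on conventional oxygen, and failure rests on respiratory rate, SpO2, pH, consciousness and ROX, not on PaO2/FiO2 below 100. Stopping on the observed reading, with the fitted random-slope model also generating the data, favours that model. This stands. When stopping followed the underlying value instead of the noisy reading, the random-slope model fell to 51 against 56. Day 7 is also a chosen day: on day 3 of set-up A about 90% or more were still observed in each arm, and the difference seen was 20 against 24.

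**Imputation helps.** Mid-trial discharge counts as withdrawal, so some recoverers are covered. Patients who terminate but stay in hospital, or who are escalated or die, are not.

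**Detail belongs in an SAP.** Working correlation and weighting do. The choice of ANOVA or GEE by data completeness is already stated in the protocol.

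**A tempting stronger reading** is that the plan compares only patients still on treatment and will hide a real benefit. The documents do not support that. GEE uses days before exit, and differential exit can create a difference as well as shrink one.

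**Conclusion.** The point holds in a limited form. Series length depends on outcome by design, the two named methods do not allow for that, and the imputation rule does not reach most of the patients concerned. Estimates of within-group change, and any arm contrast built on them, can be biased in either direction.

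The size in this trial is unknown. On the assumed inputs above, true day-7 differences of 28 to 58 mmHg appeared as 2 to 43 under the planned methods. These figures show that the bias can be large and are not a forecast; early days are affected much less. After death or intubation the true value in the simulation is itself hypothetical.

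A reader might infer that the main result is at risk. It is not: ventilator-free days, 28-day mortality and 28-day intubation are not cut off at termination. The trial also calls itself exploratory. The change should be made, but the trial does not depend on it.

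**What to change.** Replace the choice between repeated-measures ANOVA and "generalised estimating equation based on the integrity of the data" by one pre-specified analysis:

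1. A likelihood-based mixed model on all observed days within a common, early fixed window.
2. Day as a factor with unstructured covariance, or a random intercept and slope. A random intercept alone is not enough: it gave 44 against a true 58, no better than exchangeable GEE.
3. An explicit between-arm contrast at a named day.
4. The last reading before termination kept in the data, since the missing-at-random assumption rests on it.
5. The numbers recovered, escalated or dead by each day, by arm, shown beside the estimates.
6. A sensitivity analysis such as a ranked composite that places recovery, noninvasive ventilation, intubation and death.

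The cost is a change of analysis wording and some programming, with no new data and no change to patient care. The downside is that the model assumes missing at random and implies hypothetical values after death or intubation, which is why item 6 is needed. The wording should be settled before anyone analyses these outcomes by arm.

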### Recruitment

From June 2022 to March 2025, clinical staff will screen inpatients based on the eligibility criteria. If the patients meet the criteria, trained researchers will recheck and confirm their eligibility. Then inform the patients about the purpose and methods of the study, the risks and benefits of participating, their rights, and the safety and security measures taken during the trial through standardised communication that is easy to understand (Additional file 2). They will then obtain patients’ informed consent (Additional file 3). The patients will then be randomly assigned to three groups and instructed to take their assigned positions as soon as possible.

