### Experimental groups

The prone position group (Group A) will take the prone position on a horizontal bed for at least 1 h each time. Patients will be encouraged to take the position as many times as possible each day and remain in the prone position as long as possible each time if they are not tired. The investigators will insert a U-shaped pillow under each patient’s neck or chin and rectangular pillows under their shoulders, chest, hips, knees, and ankles. Then adjust the pillows to ensure their cervical and lumbar vertebrates are in functional positions and patients feel comfortable. Patients’ posture and pillow position can be adjusted at any time with anyone’s help. However, the patients must always keep the abdominal side down and parallel to the bed surface. (More details are provided in Additional file 4).

The lateral group (Group B) will be instructed to alternate lying on each side of their body at an 80°–90° angle on a horizontal bed for at least 1 h each time. Patients with a mono-lateral lung infection will be instructed to lie on the healthy side. Patients will put their upper arms and legs on quilts or pillows placed on the facing side. Their hips will be decompressed to prevent pressure injury. And they will be encouraged to lie on the same side for as long as possible each time and switch to the other side or take the supine position when they feel tired. One round is completed when the patients return to the semi-recumbent position for more than 10 min.

Patients in experimental Groups A and B will be told to change positions at least 1 h after a meal. We track the number of rounds and durations of each round for each assigned position on a daily basis. Only when the patient meets the standards of the corresponding position, and keeps it at least for 1 h at a time, will the duration be considered valid and recorded. Blood gas analysis will be performed daily and 1–2 h after returning to a semi-recumbent position on the first day.

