### Control group

Patients in the control group will take the semi-recumbent position (with the bed head elevated 30°–40°) which is the regular position taken by patients. Nurses will routinely instruct the patients to roll over and check vital signs every 2 h. Arterial blood gas will be measured daily. Patients in this group will not take the prone or lateral position unless their doctors think it is necessary.

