### Outcomes

#### Primary outcomes

The primary outcome variable is ventilator-free days in 28 days. It is defined as days free from invasive mechanical ventilation or noninvasive ventilation within 28 days after randomisation.

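### Treatment failure is counted only after the assigned position has been taken, so on a literal reading the count starts later in the prone and lateral arms than in the control arm

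*Protocol article*

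**What the plan says.** Under Secondary outcomes, treatment failure is "defined as patients who receive noninvasive, invasive ventilation or die after taking assigned positions". No time window is attached.

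Two other outcomes name randomisation as their start. The primary outcome is "days free from invasive mechanical ventilation or noninvasive ventilation within 28 days after randomisation", and 28-day mortality is "defined as death caused by all kinds of diseases within 28 days after randomisation".

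The positions are reached differently. The Control group section says "Patients in the control group will take the semi-recumbent position" and describes it as the one "which is the regular position taken by patients". Under Recruitment, randomised patients are "instructed to take their assigned positions as soon as possible", with no stated maximum delay. Under Experimental groups there is a timing condition for the prone and lateral arms alone: "Patients in experimental Groups A and B will be told to change positions at least 1 h after a meal". The same section treats a period in position as valid, and records it, only once it has lasted an hour.

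**The concern.** An outcome in a randomised comparison should start at the same moment in every arm. Here it starts at an event after randomisation, and that event comes at different times by arm. A control patient has in effect taken the assigned position when randomised, so every later failure counts. A prone or lateral patient who is ventilated or dies before being moved has not failed after taking the position. A patient who is never moved cannot fail at all under this wording.

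The failures lost are therefore lost from the experimental arms only, and both would look better than control with no true effect. If such patients stay in the analysis as non-failures, this is immortal-time bias. If they are removed, it is selection after randomisation. The outcome combines ventilation with death, so a reader would take it as a summary of clinical benefit.

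**Working it through.** **1. Start of counting.** The article states no expected rate or sample size for treatment failure, so there is no figure of its own to reproduce. The comparison is of definitions.

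| Outcome | Start stated | Same start in all arms? |
|---|---|---|
| Ventilator-free days | Randomisation | Yes |
| 28-day mortality | Randomisation | Yes |
| Treatment failure | Taking the assigned position | No: in effect at randomisation for control, later for prone and lateral |

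**2. Who is affected.** Two kinds of experimental patient are affected: (a) those who fail between randomisation and first positioning, and (b) those never positioned for any other reason. If taking a position means holding it for the hour that makes it valid, patients who give up within that hour join group (b); the article does not say. Nor does it say whether any of these patients are scored as non-failures or leave the denominator.

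**3. Illustration: never-positioned patients.** Inputs:
- Failure rate p = 0.48 in every arm with no true effect. This is the failure rate under high-flow oxygen cited in Background and rationale. Applying it here is an assumption.
- q = share of experimental patients never positioned. The article gives no value, so 2%, 5% and 10% are assumed.

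*Scored as non-failures, with the same prognosis as everyone else.* Observed rate = p(1 − q), difference = pq, relative risk = 1 − q.

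| q | Observed rate | Difference | Relative risk |
|---|---|---|---|
| 2% | 0.48 × 0.98 = 47.0% | 1.0 point | 0.98 |
| 5% | 0.48 × 0.95 = 45.6% | 2.4 points | 0.95 |
| 10% | 0.48 × 0.90 = 43.2% | 4.8 points | 0.90 |

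*All of them removed from the denominator, same prognosis.* Observed rate = 0.48(1 − q)/(1 − q) = 0.48, so the relative risk is 1.00 for any q. Bias then needs never-positioned patients to differ in prognosis.

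**4. Illustration: failures before positioning.** Patients in group (a) do differ, because all of them failed. Let f be the share of experimental-arm failures that occur before positioning (also assumed). If these patients are scored as non-failures, the table above applies with f in place of q. If they leave the denominator, the observed rate is 0.48(1 − f)/(1 − 0.48f):

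- f = 2%: 0.4704/0.9904 = 47.5%, difference 0.5 points
- f = 5%: 0.456/0.976 = 46.7%, difference 1.3 points
- f = 10%: 0.432/0.952 = 45.4%, difference 2.6 points

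**5. Effect on a test.** Take 583/3 ≈ 194 patients per arm and an unadjusted two-sided 5% comparison of one experimental arm with control. The chance of a false finding in favour of the experimental arm should be 2.5%. It is approximately Φ(δ/SE − 1.96), where δ is the spurious difference. For q = 5% scored as non-failures, SE = √[(0.48 × 0.52 + 0.456 × 0.544)/194] = 0.0507, and Φ(0.024/0.0507 − 1.96) = 6.9%. For 2% and 10% it is 3.8% and 15.6%. Under the removal rule in step 4 it is 3.1%, 4.4% and 7.5%.

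**The case against.** The best defence is that the phrase is loose shorthand in a condensed article for failure after allocation to a position. Data collection and management gives a general window, with outcomes measured during the intervention and at 28 days after enrolment, and says that data on withdrawn patients are collected. Nothing says outright that never-positioned patients are dropped or scored as successes. However, a general measurement window does not override the specific definition of this outcome. If the authors meant randomisation, the sentence should say so, as it does for mortality in the same list.

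The second defence concerns size, and it largely stands. The exclusion criteria remove patients who need immediate intubation and those who cannot or will not lie in the study positions. Positioning is meant to start promptly, the wait after a meal is short, and there are measures to support adherence. Few events may fall in the gap. Only one secondary outcome of an exploratory trial is affected. Its components also appear in the primary outcome and in mortality, both counted from randomisation.

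A reader might infer three stronger points that the article does not support:
- *That the definition contradicts the intention-to-treat statement.* That sentence, in Methods for additional analyses, concerns missing values of withdrawn patients and does not set when an outcome starts. The definition fits poorly with an intention-to-treat comparison, but no sentence is contradicted.
- *That every other 28-day outcome runs from randomisation.* This is explicit for the primary outcome and mortality; the 28-day intubation rate names no start.
- *That the 20% dropout allowance shows how many patients will never be positioned.* It does not. The withdrawal criteria include refusal partway through, early discharge and refusal of high-flow oxygen, and many such patients will already have taken the position.

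**Conclusion.** The point holds as a defect in one outcome definition. As written, the start of counting depends on the arm, and any failures lost are lost from the prone and lateral arms. If those failures are scored as non-failures, the direction is known: it favours the experimental arms. If all never-positioned patients are removed, the result depends on their prognosis, and it favours the experimental arms where they include early failures.

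The size is unknown and may be small. The differences of 1.0, 2.4 and 4.8 points rest on a 48% failure rate in every arm, no true effect, assumed shares of 2%, 5% and 10%, and scoring as non-failures. They show how the error scales and do not predict its size in this trial. The primary outcome, mortality and the sample size are untouched. The definition should still be corrected, because the bias is avoidable.

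**What to change.** Replace the definition with: *noninvasive ventilation, invasive ventilation or death from any cause within 28 days after randomisation, in all randomised patients, whether or not the assigned position was taken*. If a version counted from first positioning is wanted, keep it only as a supplementary per-protocol analysis, labelled as such.

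The cost is one sentence. The primary outcome already requires both forms of ventilation from randomisation, deaths are recorded at Day 28, and data on withdrawn patients are already collected. No new data or change to the sample size is needed.
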